#### Regarding adverse reactions

-It has been widely recognized the adverse reactions of interferon therapy, none of them have been associated until now to the use of any therapeutic vaccination under study, including NASVAC.

### **3. Ethics and Medical Deontology**

#### **General ethical considerations**

The trial is justified from the ethical point of view because:

- The study is carried out according to the principles of the Declaration of Helsinki on investigations with human beings for therapeutics purposes. The patients will receive the medical care and the normal general treatment that is applied in these cases.
- CHB is a slow developing disease. The fact of being 6 – 12 months without any of the specific recognized treatments will not affect significantly the patients' evolution. Besides, follow-up will be very cautious and upon any sign of disease progression, the patient will be withdrawn from the study treatment and given a recognized specific anti-hepatitis therapy (interferon alpha or Lamivudine). In all cases patients included in the trial, after its completion will receive one of these treatments, if the principal patient and investigator decide.

- It is possible that the patients obtain benefit from their participation in the study since there are reasonable evidences that vaccination can improve their condition according to phase I results.
- Treatment of CHB patients with NASVAC, according to the results obtained at CIGB, does not represent additional risk for the patients. It is a quite safe intervention, with a very low probability of associated adverse reactions. Doctors can properly treat the possible adverse reactions and a favorable risk-benefit balance justifies them.
- Written consent of individuals will be requested, after properly informing about the objectives of the investigation, treatment to be subjected and possibility to refuse to participate in the trial at any moment without consequences to his medical care. When publishing, the confidentiality of the individuals' personal data will be guaranteed.
- All patients unable to satisfactorily control the viral load will be treated with available antiviral drugs, according to their physician decision, independently whether they belong to the control or treatment groups.
- There are preliminary evidences of safety and efficacy after the first clinical trial using NASVAC in chronic hepatitis B patients, conducted in Dhaka, Bangladesh, as previously described in the present protocol.

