### **5.5 Exit criteria or interruption of the treatment after inclusion**

- Voluntary abandonment of the patient.
- Appearance of any of the above-mentioned exclusion criteria.
- Patients with worsening of the liver pathology in comparison with baseline levels, according to the investigator's criteria.
- Severe adverse reactions according to WHO guidelines
- Feverish status (more than 37.8 °C) at the moment of vaccine administration or in the 24 hour before, or any suspected or confirmed infectious diseases that results in the suspension of three vaccine administrations during the course of the immunization schedule.
- Patient's death.

Patients, once included, will be considered in the analysis even if they interrupt the treatment. Therefore, no case report form will be eliminated.

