### Rules for the use of concomitant treatments

- Any specific anti hepatitis treatment should be avoided, as well any other investigational drug.
- Other drugs that can affect the immune system should also be avoided (corticosteroids, immune-suppressors, immune-stimulants, cytokines, etc.).

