## Evaluation of the viral infection markers and statistic hypothesis

**HBV-DNA:** Response: Undetectability of HBV DNA in the serum of infected patient by using a quantitative PCR assay with 250 copies/mL as a viral detection limit of sensitivity at the end of therapy with NASVAC TVC as well as in every study cut starting from dose number five and ending at one year after treatment started.

The success criteria will be assessed one year after study started however it can be evaluated for Interim Analysis according to the date of virological assessment.

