### **Statistical hypothesis**

It is expected that the administration of NASVAC TVC, as defined in the present protocol, to chronic hepatitis B patients, will improve the specific anti-HBV immune response of treated patients and consequently will significantly increase the percentage of patients reducing the viral load to undetectable levels after treatment completion compared to the group administered with Pegylated Interferon, expecting a difference between groups of more than 20%.

H0: Equivalency in the percentage of chronic hepatitis B patients reducing the viral load to undetectable levels. Formally,  $H_0: \delta \leq \delta_0 = 0.20$  where  $\delta$  represents the difference between viral seronegativization, based in quantitative PCR assay with a sensitivity of 250 copies/mL, in the group treated with NASVAC compared to the group treated with Interferon.

H1: Superiority in the percentage of chronic hepatitis B patients reducing the viral load to undetectable levels. Formally,  $H_1: \delta > \delta_0 = 0.20$  where  $\delta$  represents the difference between viral seronegativization, based in quantitative PCR assay with a sensitivity of 250 copies/mL, in the group treated with NASVAC compared to the group treated with Interferon.

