### **Interim analysis**

After 5 and 10 administrations and also at 48 weeks, patients will be tested by PCR to quantify HBV DNA in serum as well as for HBsAg and HBeAg seroconversion. A comparative study will be conducted for the same variables for internal comparisons between both groups in order to have a reference to standard treatment with a recognized efficacy.

a) A 20% superior percentage of viral load reduction to undetectable levels in the group treated with NASVAC compared to PegIFN treated group in any of the virological study cuts will be considered as a success criteria for the Interim Analysis.

b) A superior difference in the proportion of patients with ALT normalization or combined ALT normalization and viral load reduction to undetectable levels at a defined time (5, 10 dosis or 48 weeks) between groups will be considered a success criteria for the Interim Analysis.

e) A sustained biochemical (ALT) response during three consecutive determinations after dose number 10 will be considered a success criteria.

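### Response is scored on HBV DNA or ALT alone, so a patient given rescue antiviral therapy on study can count as a responder for the assigned arm

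*Protocol*

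**What the plan says.** **Rescue.** Protocol section 3, General ethical considerations, states that "upon any sign of disease progression, the patient will be withdrawn from the study treatment and given a recognized specific anti-hepatitis therapy", with interferon alpha or lamivudine as the drugs. The following sentence deals separately with treatment after trial completion. A later bullet in the same list provides for available antivirals, at the physician's decision and in either arm, when viral load is not satisfactorily controlled. It gives no timing.

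**Analysis population.** Section 5.5: "Patients, once included, will be considered in the analysis even if they interrupt the treatment".

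**Concomitant treatment.** Section 6: "Any specific anti hepatitis treatment should be avoided, as well any other investigational drug". No consequence for scoring follows.

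**Response.** Section 10, Evaluation of the viral infection markers: "Undetectability of HBV DNA in the serum of infected patient by using a quantitative PCR assay with 250 copies/mL", at the end of NASVAC therapy and at the study cuts from dose five to one year. Then: "The success criteria will be assessed one year after study started".

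**Interim success.** Section 10, Interim analysis, criterion a: a 20% advantage in undetectability "in any of the virological study cuts will be considered as a success criteria for the Interim Analysis". Criterion b uses ALT normalisation, alone or combined with undetectability. Criterion e uses sustained ALT response.

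**Hypothesis.** NASVAC "will improve the specific anti-HBV immune response of treated patients and consequently will significantly increase the percentage of patients reducing the viral load", with an expected difference from pegylated interferon of more than 20%.

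**The concern.** Three rules that the protocol does fix (rescue is allowed, everyone stays in the analysis, response is a laboratory value alone) combine into a scoring rule that it never states: clearance after a rescue drug is credited to the randomised arm. The hypothesis concerns clearance that follows from a vaccine-induced immune response, and clearance caused by lamivudine or interferon alpha is not that effect. In the NASVAC arm, one of the named rescue drugs belongs to the comparator's class.

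At stake is the contrast that decides success, a difference judged against 20 points. The trial is open label, and the two arms end treatment at different times (Week 24 for vaccine, Week 48 for interferon in the assessment table), so equal rescue in the two arms cannot be taken for granted.

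**Working it through.** **Step 1. Is rescue on study?** Yes, for the progression rule. It withdraws the patient from study treatment, while post-completion therapy has its own sentence. Where the protocol means leaving the trial it says so, as for severe adverse events in section 8. The uncontrolled-viral-load bullet may apply on study, after it, or both.

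**Step 2. Does the rescued patient stay in the analysis?** Yes, under section 5.5, which also lists worsening liver pathology among the reasons for exit or interruption.

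**Step 3. Does any response rule exclude rescue?** No. Neither the HBV DNA definition nor interim criteria a, b and e mention other therapy. Section 6 governs conduct, not scoring.

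**Step 4. Is the patient still tested?** Not certain. Section 7 says patients who abandon the trial are evaluated unless contact is lost, but does not promise HBV DNA at one year. The miscount needs such a test.

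**Step 5. Weight of one patient.** The protocol gives two group sizes.

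- 80 per arm (section 4): 100/80 = 1.25 points
- 60 per arm (section 10, Number of patients): 100/60 = 1.67 points

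**Step 6. Illustration under rare rescue.** The protocol has no figure of its own to reproduce here. Scored rate = p + (1 − p) × r × s, where

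- p is the true response rate: 50% for NASVAC (section 2.7, month-12 result of the earlier patient study) and 30% for pegylated interferon (section 2.4, a general figure for current treatments, not specific to HBV DNA);
- r is the share of non-responders rescued: 1 to 3%, **assumed**. Low values are plausible because section 3 says "CHB is a slow developing disease";
- s is the share of rescued patients who become undetectable: 30% (the same section 2.4 figure) or 80%, both **assumed**.

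| r NASVAC / r PegIFN | s | NASVAC | PegIFN | Difference | Shift from 20 |
|---|---|---|---|---|---|
| 3% / 1% | 30% | 50.45 | 30.21 | 20.24 | +0.24 |
| 1% / 3% | 30% | 50.15 | 30.63 | 19.52 | −0.48 |
| 3% / 3% | 30% | 50.45 | 30.63 | 19.82 | −0.18 |
| 3% / 1% | 80% | 51.20 | 30.56 | 20.64 | +0.64 |
| 1% / 3% | 80% | 50.40 | 31.68 | 18.72 | −1.28 |

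Example, first row: 0.50 + 0.50 × 0.03 × 0.30 = 0.5045, and 0.30 + 0.70 × 0.01 × 0.30 = 0.3021.

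In patients at 80 per arm, NASVAC has 40 non-responders, so 0.4 to 1.2 are rescued. PegIFN has 56, so 0.56 to 1.68 are rescued. That is about one patient per arm.

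**The case against.** The strongest reply is that this is silence rather than error. Section 5.5 settles who is analysed, not how they are scored, and is compatible with non-responder scoring. An analysis plan that is not shown could supply the rule. Using outcomes regardless of rescue is also a recognised intention-to-treat approach. Part of this stands: no sentence says outright that a rescued patient is a responder. But the protocol does define response, and applied literally that definition gives this result. Nor does it say that outcomes regardless of rescue are intended, which would fit poorly with a hypothesis about the vaccine's immune effect.

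The pathway is also narrower than it first appears, and these limits stand:

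- The hypothesis refers to undetectability after treatment completion, which a patient withdrawn for progression has not reached.
- The HBV DNA definition may require undetectability at every cut. If so, a late rescue fails there and could count only under interim criterion a.
- HBV DNA testing after exit is not clearly promised.

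Three stronger readings are tempting but unsupported.

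- A reader might infer that the gap from Week 24 to one year gives ample time for NASVAC patients to be rescued under the progression rule. That rule literally covers patients still on study treatment. Only the untimed viral-load bullet could reach that window, and it may partly mean post-trial care.
- A reader might assume heavy rescue. With 30% of NASVAC and 10% of PegIFN non-responders rescued and s = 30%, 20 points reads as 22.4; with the reverse, 15.2. Nothing in the protocol supports such rates.
- A reader might infer that the rule favours NASVAC. The direction depends on which arm is rescued more, and equal rescue slightly reduces the difference in this model.

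**Conclusion.** The point holds in limited form. As written, a patient rescued on study who is still tested and is undetectable counts as a responder for the assigned arm, and the ALT criteria have the same gap. The size and direction of the bias are unknown because no rescue rate is given. The assumption-free figure is 1.25 points per such patient at 80 per arm, or 1.67 at 60. If 1 to 3% of non-responders are rescued, the illustrative 20-point difference moves by about 0.5 point, or up to 1.3 if 80% of the rescued clear. Those shifts rest on assumed rescue and clearance rates and on true rates of 50% and 30% borrowed from the background sections. Minor to moderate: a cheap improvement, not a threat to the trial's conclusion on anything the protocol shows.

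**What to change.** Add one sentence to the HBV DNA response definition in section 10, and refer to it from interim criteria a, b and e: a patient who starts any anti-HBV drug other than the assigned one before an assessment is a non-responder from that date, whatever the later HBV DNA or ALT. Check that the case report form records the drug and its start date. All patients stay in the analysis, and who receives rescue, and when, does not change.

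The cost is one sentence, a cross-reference and the form check. Stated response rates fall slightly where rescue occurs. With 1 to 3% of non-responders rescued and 30% of those clearing, the fall is 0.15 to 0.45 point for NASVAC (0.50 × r × 0.30) and 0.21 to 0.63 point for PegIFN (0.70 × r × 0.30).

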#### **Trial authorization and approval**

The trial will be carried out in agreement with the regulations established in Bangladesh.

The protocol will be approved by the Ethical Committee of the Faculty of Medical Sciences related Hospital and other relevant authority of Bangladesh.

#### **Explanation on how the patients will be informed and their consent will be obtained**

The patients will receive explanation about their disease and the characteristics of the trial, objectives, prospective benefits, risks and inconveniences that could be presented related with the treatment. The potential advantages of the proposed treatment and possible adverse effects will be explained to the patient or relatives, specifically the medical and nursery cares required for these cases.

The patients will decide on their participation in the trial freely, through written consent (see Annex 2), in case of abandonment of the treatment by self-decision, their medical care will not be affected.

## 4. General design

**Type of trial:** Open phase II-III clinical trial.

### **Design of the trial**

The population sample to be tested will be of 160 CHB patients, with variable serum transaminase levels, without treatment for at least 6 months, selected according to inclusion and exclusion criteria and allocated in two study groups (SG). The first study group, SG1 will include 80 CHB patients (HBeAg (+) and HBeAg (-)) that will be treated with 1 mL NASVAC (100 mcg per antigen, per dose per patient), administered in two cycles of inoculations, the first one by the intranasal route with five intranasal inoculations every 14 days each. During the second cycle patients will receive the same dosis (100 mcg per antigen) by the intranasal route and additionally the same dosis by the SC route,

The SG2 will be treated with Alpha-Interferon at standard dosis (weekly injection by SC route).

The treatment is discontinued for all patients of SG1 after completion of both cycles. The evaluation will continue during one year, but an interim report will be released after 5 and 10 administrations.

During the whole treatment period up to one year from the beginning of treatment, the systematic assessment of patients is launched to determine to what extent the treatment has driven them to generate the capacity to control the HBV load. This information is included in Figure 1.

[figure not shown]

**Figure 1.** General Algorithm of the trial

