New properties arise from the mixture of HBsAg and HBcAg as a consequence of the adjuvant and immune-modulating actions of both antigens. Nasal administration of both antigens in a combined formulation induces a heightened humoral and cellular immune response against both HBsAg and HBcAg.

Previous positive although still weak therapeutic effect in the literature using commercially available HBsAg-based vaccines and the higher immunogenicity of the CIGB HBsAg, along with the opportunity of generalized immune response after mucosal immunization, deserve a refined approach for evaluation in patients.

The present first controlled clinical trial in patient with the HBV surface and core antigens is intended to determine any therapeutic potential on chronically HBV infected patients.

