Virological response was assayed after five and ten doses. The HBeAg negative group of patients behaved better in terms of HBV elimination by quantitative PCR (detection limit 250 copies/mL) compared to HBeAg positive group. From 13 HBeAg patients receiving five intranasal doses of NASVAC, six patients reduced the viral load to undetectable levels for 46% just after five intranasal doses. None of the six patients clearing the virus were over the ULN for ALT after the fifth or after dose number 10, even when four of them had a mild ALT flare during the first cycle of IN administrations, suggesting a quick immune response. The absence of ALT increase during treatment in two patients clearing the virus suggests that non-cytolytic mechanisms were also activated. For patients clearing the virus, ALT increases ranged between 1.5 and 3 times the ULN, such increases where in one or two consecutive determinations only, suggesting that the potentially curative effect of vaccination was associated at least to small and quick flares of ALT levels. Such increases were not clinically apparent as patients didn't report any adverse event during the course of the vaccination, and physicians didn't detect any related symptom, suggesting that the increases in ALT levels were not clinically apparent. Also, due to the temporal relation to the starting date of the protocol, it is reasonable to predict that it was associated to the vaccination. From literature is known that specific immune stimulation has been related to ALT increases and virological response in CHB patients.

In support of the results obtained after the end of treatment, the evaluation of the 6 month time follow up (time 12 months) evidenced a further decrease in the levels of HBV DNA to undetectable levels in 50% of total patients, being outstanding the behavior of HBeAg negative patients that reduced the viral load in 8 of 13 patients. HBeAg positive patients also evidenced strong reductions in viral load however the reduction to undetectable was reduced compared to HBeAg negative patients, which is understandable based in the fact that the baseline viral load values were much higher for HBeAg positive patients. For both groups ALT values evidenced a generalized normalization reaching 100% at month 9 and 95% at month 12..

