##### **Control variables**

- Age
- Sex

- Weight
- Body mass index
- Duration of the disease
- Initial viral load
- Smoking and other toxic habits

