### **Serology: Response:**

**HBeAg: Negativity:** disappearance from serum

**Seroconversion:** disappearance of HBeAg from serum and appearance of HBeAb.

**HBsAg: Negativity:** disappearance from serum

**Seroconversion:** Appearance of HBsAb in serum.

Both groups will be compared according to the categories defined above by the chi-square test or odds ratio calculation. A logistic regression will be also performed for a multivariate analysis of the influence of the different control variables that result significant in the previous univariate analysis. A signification level of  $p = 0.1$  will be considered. The potency will be of 80%.

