## **11. Practicalities**

### **Detailed plan. Subject management**

Patients from the Gastroenterology outpatient consultation potentially can participate in the protocol. These sessions should take place at least once per week and the following steps will be taken with every patient that fulfills the inclusion criteria:

- Clinical examination by specialists.
- Laboratory analyses
- If the patient fulfills the rest of the inclusion criteria and does not have any of the exclusion criteria, his written consent is requested after the proper explanation.
- The individual data form will be filled.
- The patient will receive an explanation about the treatment and its time of duration.
- The day before the beginning of treatment, serum samples will be taken for the baseline data.
- The injections will take place every fortnight at the clinic. Clinical examinations will be done according to the established schedule.
- At each evaluative consultation the appointment for the next one will be established.

For the purpose of quantitative HBV-DNA determinations, the serum samples will be taken at the consultations and kept frozen until their transportation to laboratory. HBV-DNA determination for inclusion will be the same method to the one to be used during assay.

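### The protocol text describes no random assignment to the two open arms, and HBeAg status, which the protocol itself treats as prognostic, is neither balanced by design nor a control variable

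*Protocol*

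**What the plan says.** Section 4 of the protocol describes the study as "Open phase II-III clinical trial". Under Design of the trial, patients are "selected according to inclusion and exclusion criteria and allocated in two study groups (SG"). The NASVAC arm takes both HBeAg types ("SG1 will include 80 CHB patients (HBeAg (+) and HBeAg" (-)), but no proportion is fixed for it, and the HBeAg mix of the interferon arm is not mentioned. Elsewhere, at the end of the preclinical immunogenicity section, the study is called controlled ("The present first controlled clinical trial in patient with the HBV surface and core antigens"), not randomised.

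Section 11 (Detailed plan. Subject management) lists what happens to each patient. After eligibility is confirmed, "If the patient fulfills the rest of the inclusion criteria and does not have any of the exclusion criteria, his written consent is requested"; then come the data form, the explanation of treatment, baseline sampling and the injections. No step assigns an arm. The table of forms in section 9 has screening, inclusion and administration records, but no assignment list or envelope.

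On prognosis, the clinical experience in section 2.7 reports that at month 12 half of all pilot patients were undetectable, singling out "HBeAg negative patients that reduced the viral load in 8 of 13 patients". It links the weaker result in HBeAg-positive patients to their much higher baseline viral load.

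Section 7 lists seven control variables. "Initial viral load" is one; HBeAg status is not, and appears only as an outcome marker. In section 10 the groups are compared by chi-square or odds ratio, and a logistic regression takes in those "control variables that result significant in the previous univariate analysis".

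**The concern.** The trial aims to show superiority over interferon on undetectable HBV DNA. That claim needs arms that are comparable at baseline. In an open trial with no stated method of assignment, nothing in the text prevents the expected treatment, or the patient's apparent prognosis, from influencing which arm a patient joins.

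HBeAg status is the obvious route. It is known before entry, because the inclusion criteria set different thresholds for HBeAg-positive and HBeAg-negative patients, and the protocol's own pilot links it to the primary outcome. If one arm held more HBeAg-negative patients, it would look better with no drug effect. The planned adjustment omits HBeAg and admits its nearest proxy only conditionally. Assignment cannot be repaired after enrolment, so the place to settle it is the protocol. An analysis plan written later would not instruct the sites.

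**Working it through.** **Pilot figures (section 2.7).** There were 13 HBeAg-negative and 7 HBeAg-positive patients, 20 in all.
- HBeAg-negative: 8/13 = 61.5%.
- All patients: 50% of 20 = 10 responders.
- HBeAg-positive, by subtraction: 10 - 8 = 2, and 2/7 = 28.6%. This is not printed and assumes all 20 were evaluable at month 12. Were only 18 evaluable, it would be (9 - 8)/5 = 20%.
- Gap: 0.615 - 0.286 = 0.330.
- Precision: exact 95% intervals are 32% to 86% and 4% to 71%; Fisher p = 0.35. The gap serves as an illustration and is not an established effect.

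**Spurious difference.** Bias = imbalance in HBeAg-negative share × 0.330. The imbalances are assumed; the protocol gives none.
- 20 points: 0.20 × 0.330 = 0.066.
- 30 points: 0.30 × 0.330 = 0.099.
- Imbalance needed for a full 20-point difference: 0.20/0.330 = 61 points.

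**Comparison with chance.** With 80 per arm and 65% HBeAg-negative (the pilot mix), simple randomisation gives an SD of imbalance of sqrt(2 × 0.65 × 0.35/80) = 0.075, so 95% of imbalances lie within ±14.8 points (±4.9 points of bias). Imbalances of 20 and 30 points are about 2.7 and 4 SDs. They would point to selection more than to chance.

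**Effect on decisions.** Assume no drug effect, pilot rates in both arms and 80 per arm. The arm rates are then 53.3% v 46.7% (20 points) or 54.9% v 45.1% (30 points). The pooled standard error is sqrt(2 × 0.5 × 0.5/80) = 0.0791; the unpooled ones are 0.0789 and 0.0787.

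1. Test of zero difference, two-sided 0.10 (the level stated in section 10; taking it as two-sided is an assumption). The critical difference is 1.645 × 0.0791 = 0.130.
   - 20 points: upper tail beyond (0.130 - 0.066)/0.0789 = 0.81, plus a small lower tail, gives 21.5%.
   - 30 points: upper tail beyond (0.130 - 0.099)/0.0787 = 0.40, plus a small lower tail, gives 34.8%.
   - No imbalance: 10%. With 60 per arm the two figures are 18.6% and 28.9%.
2. Raw 20% interim criterion (Interim analysis, section 10), at a single cut.
   - 30 points: beyond (0.20 - 0.099)/0.0787 = 1.28, about 10%.
   - No imbalance: beyond 0.20/0.0791 = 2.53, about 0.6%.
3. Declared null (difference at most 0.20), one-sided 0.10.
   - 30 points: beyond 1.28 + 1.28 = 2.57, about 0.5%.
   - 20 points: beyond 1.28 + (0.20 - 0.066)/0.0789 = 2.98, about 0.1%.

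The 80 per arm comes from Design of the trial and the 60 from Number of patients. Those sections disagree, which is a separate matter.

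**The case against.** Four objections have force.

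**Silence is not proof.** A reader might infer that the trial is not randomised and that the investigator picks the arm. The documents do not support that. The word open describes masking, no passage gives the investigator the choice, and neither Figure 1 (the general algorithm) nor the contents of the annexed forms can be seen. What stands is that the text describes no random method. Even if the figure used the word, the design paragraph and the subject-management steps would still need the method, timing and concealment.

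**Some adjustment exists.** A reader might infer that no later analysis could detect or correct an HBeAg imbalance. That goes too far. Initial viral load is a listed control variable, and the protocol ties the HBeAg difference to it. HBeAg is measured, and section 10 applies exploratory analyses to all study variables. What stands is that the proxy is partial and enters only through a significance screen.

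**The pilot gap is weak evidence.** It rests on 20 patients, one figure is derived, and it was seen only under NASVAC. The protocol nevertheless treats HBeAg as prognostic.

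**Covariate choice often sits in an SAP, and stratification is not a condition of validity.** Both are true. Ordinary chance imbalance is already covered by the test's error rate. But the protocol does fix a method here: a covariate list without HBeAg and a univariate screen, which is worse than fixed terms using data already collected.

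**Conclusion.** The point holds in limited form. The protocol text gives no random assignment, no sequence and no concealment for an open two-arm superiority comparison. The one baseline factor it describes as linked to the outcome, apart from viral load, is neither balanced by design nor adjusted for directly.

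A reader might infer that HBeAg imbalance alone could produce the claimed 20-point advantage. It would take about 61 points of imbalance, which is implausible, and the declared null would be wrongly rejected in under 1% of trials at a 20- or 30-point imbalance. The exposure lies elsewhere. A test of zero difference would have its 10% error rate raised to about 21% or 35%. The raw interim criterion would be met about 10% of the time at a 30-point imbalance, against about 0.6% with none.

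These figures rest on the pilot gap being real and equal in both arms, on assumed imbalances, and on 80 per arm. They cover HBeAg only; selection on unmeasured factors would add to them, and no covariate model would remove it.

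**What to change.** **Assignment.** In section 4 (Design of the trial), and as a step in section 11 (Subject management) after consent and baseline sampling, state that patients are assigned 1:1 from a computer-generated list stratified by HBeAg status. Block sizes should be varied and undisclosed, and the list concealed from the enrolling investigators. In an open trial, known fixed blocks would let later assignments be guessed. If Figure 1 already shows randomisation, the text should be brought into line with it.

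**Analysis.** Add HBeAg status to the control variables in section 7. In section 10, make the primary comparison of undetectable HBV DNA adjusted for HBeAg status and baseline log10 HBV DNA as fixed terms, and remove the univariate screen.

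**Cost.** A list, a concealment procedure and protocol wording. HBeAg and HBV DNA are already needed for eligibility, and no patients are added. The downside is a small administrative load.
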